### Expense allowance

Adolescents participating in our study receive a gift voucher of €50 as an expense allowance for participation.

### Adverse event reporting and harms

We expect no adverse events caused by participating in our study. Medically indicated treatments will not be postponed or changed because of participation. Any serious aggravation of depressive or any other symptoms will result in drop-out and therapeutic assistance if needed. Participants and legal guardians can end study participation at any time without giving reasons, if they no longer wish to participate.

### Statistical analysis

Data will be collected in accordance with the current standard of empirical research. Data will be evaluated with IBM SPSS Statistics version 25.0 for Windows (released 2017; IBM Corp, Armonk, New York). First, depending on the distribution of control variables, differences between the adolescents with depression and the control group will be computed via *t*-tests or Mann–Whitney *U*-tests. As cortisol and alpha-amylase levels are commonly skewed, a square-root transformation will be applied to achieve a normal distribution.^64^ Cortisol and alpha-amylase measurements will be averaged over three days and entered into the repeated measures ANCOVA as the dependent variable, with group as the independent variable.

Cortisol and alpha-amylase increase will be computed by area under the curve analyses.^65^ For an additional measure of increase, delta scores will be computed between baseline and the highest value.^66,67^ To determine group differences in cortisol and alpha-amylase increase, ANCOVAs will be calculated with group as an independent variable.

To examine the relationship between subjective and objective sleep quality, depressive symptoms and cortisol/alpha-amylase increase, bivariate correlations with a false discovery rate correction will be computed.^68^ Effect sizes will be reported with Cohen's *d*, with 0.2 being considered a small, 0.5 a medium and 0.8 a large effect.

Finally, in case of non-normality distributed and sufficiently skewed outcome variables, the direction of the relationship between sleep quality and depressive symptoms will be examined with direction dependence analysis.^63^ Direction dependence analysis enables to statistically test the directional relation between pairs of variables, including observational variables, as well as adjusting for covariates that may contribute to the causal process.^69^

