## Depressive disorders in adolescence

Depressive disorders are common mental health problems during adolescence. In a survey conducted in the USA, a lifetime prevalence of about 12% was found for the adolescent sample, and prevalence nearly doubled from early (13/14 years: 8.4%) to late adolescence (17/18 years: 15.4%).^3^ Additionally, the number of adolescents with depressive symptoms is even higher when considering the high number of adolescents with subthreshold depression, with a lifetime prevalence of up to 20% at the age of 18 years.^4^

Depressive disorders during adolescence are associated with more burdensome circumstances in adulthood, including mental health problems, suicidal ideation or attempts, reduced educational attainment and economic status, lower relationship quality and higher levels of conflicts and violence.^5^ This underlines the importance of a deeper understanding of the aetiology and severity of depressive disorder.

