## Sleep disturbance in patients with depressive disorder

Sleep disturbance constitutes an important symptom of depressive disorders, and it gains even greater importance when considering that it may increase the risk of suicidal behaviour among adolescents.^6^ Delayed sleep onset and decreased sleep efficiency, combined with changes in rapid eye movement (e.g. shorter latency and increased activity, density and amount of rapid eye movement sleep) and slow-wave sleep (e.g. decreased sleep amount), are frequent findings from studies assessing sleep in adults with depression.^7^ Regarding paediatric depression, findings are far more heterogeneous. In his review dealing with sleep disturbance in paediatric depression, Rao considered 24 electroencephalogram studies conducted in children and adolescents.^7^ A prolonged sleep latency was found in eight of these studies, and 15 studies found no differences. A decrease in sleep efficiency was found in three of the studies, and 19 studies found no differences.^7^ As sleep underlies multifarious influences in the context of development, the heterogenous study situation could reflect the complexity of sleep quality and its components during the developmental period.^7^ Examination of sleep latency and efficiency via accelerometry, as conducted in this study, has been shown to be a promising approach in previous research.^8,9^

In addition to objective measures of sleep quality, the burden of impaired subjective sleep quality and sleep complaints caused by depression should be considered. Many studies in adults with depressive disorders have assessed subjective sleep quality, and findings show that over 80% of patients report sleep difficulties.^10^ Previous research showed that similar impairments can be found in adolescents with depressive disorders. Considering only subjective sleep assessments without objective sleep data, Gupta et al found impaired sleep quality, delayed sleep onset, shorter sleep duration, and a correlation of sleep quality with severity of depressive symptoms.^11^ These abovementioned impairments in subjective as well as objective sleep quality may lead to serious mental burden and an increased stress level in everyday life for many adolescents with depression; therefore, both measurements are important to consider.

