#### Inclusion criteria

Children and adolescents between 12 and 18 years are eligible for participation. A sufficient understanding of the German language, as well as informed consent of both participants and legal guardians, is required to participate in the study.

For the index group, potential participants are those with depressive disorders according to the diagnostic criteria of the ICD-10.^33^ More precisely, we include the ICD-10 codes F32.0 (mild depressive episode), F32.1 (moderate depressive episode), F32.2 (severe depressive episode without psychotic symptoms), F33.0 (major depressive disorder, recurrent, mild), F33.1 (major depressive disorder, recurrent, moderate), F33.2 (major depressive disorder, recurrent, severe without psychotic features) and F43.21 (adjustment disorder with prolonged depressive reaction) in our index group.

For the control group, we include healthy adolescents matched by gender, age and pubertal status according to the Pubertal Development Scale (PDS). This shall align age- and gender-specific differences.^34^

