### Physiological consistency of measurement

As all participants start measurements on a Sunday evening, the weekdays of accelerometry and saliva sampling stay constant over all participants. Measurement timing of female participants is aligned with the female menstrual cycle. Start of the most recent menstruation is assessed at the first study appointment, and all measurements are scheduled for the female participants’ luteal phase, as previous studies found evidence that CAR between women and men might be most similar during the luteal phase.^58,59^ Moreover, use of oral contraceptives is assessed, as this may slightly blunt the CAR.^60^

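### The correlations among sleep, symptoms and hormone increase are unadjusted, and matching does not remove age, puberty or gender gradients from them

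*Protocol article*

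**What the plan says.** **The correlations.** The Statistical analysis section states the purpose, "To examine the relationship between subjective and objective sleep quality, depressive symptoms and cortisol/alpha-amylase increase", and then the method: "bivariate correlations with a false discovery rate correction will be computed". No partial, stratified or covariate-adjusted version is given. The section does not say whether the two groups are pooled.

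**Adjustment of these relations.** It appears only as something that direction dependence analysis is able to do. That analysis is run only if outcomes are non-normal and sufficiently skewed. It covers only sleep quality and depressive symptoms, and its covariates are not named.

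**Age range and matching.** Under Inclusion criteria, "Children and adolescents between 12 and 18 years are eligible for participation". Controls are matched on gender, age and PDS status, with the purpose: "This shall align age- and gender-specific differences".

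**Relevance of these variables.** On sleep, the background section says: "As sleep underlies multifarious influences in the context of development". Under Physiological consistency of measurement, all measurements of female participants are placed in the luteal phase because "CAR between women and men might be most similar during the luteal phase". Use of oral contraceptives is also recorded.

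**Role of the correlations.** The Aims ask whether sleep changes go together with changes in cortisol and alpha-amylase. The secondary outcome concerns the relation of symptoms and stress responsiveness to sleep quality. The power section gives the correlational analyses their own sample size, N = 44.

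**The concern.** Matching makes the two groups alike in age, gender and pubertal status. It does not make the participants within a group alike. A correlation is computed over exactly that within-group spread, in which a 12-year-old boy and an 18-year-old girl are two points on the same plot.

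If two measures both move with age or puberty, they will correlate without any direct link. If they move in opposite directions, a real link can be masked. The false discovery rate correction limits the number of false discoveries among valid tests and does not remove this bias.

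At stake is how the relational aims are read. An association between, say, sleep efficiency and cortisol increase could be reported as a link between sleep and the stress axis when it is partly a developmental gradient.

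**Working it through.** **1. The article's own figure.** The correlational analyses are sized with an effect of 0.40 and 80% power, giving N = 44. Take 0.40 as a correlation, with two-sided alpha 0.05 (alpha is stated for the cortisol calculation and assumed here; sidedness is not stated). The point-biserial noncentral t model has noncentrality sqrt(N r²/(1 − r²)) = sqrt(44 × 0.16/0.84) = 2.90 with 42 degrees of freedom. It gives power 0.807, and N = 44 is the smallest N that reaches 80%. The figure is reproduced. The article labels the 0.40 as d, but 44 follows only if it is an r, and it is used as an r below.

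**2. Inputs that the article does not give.** No correlation of any study variable with age, puberty or gender is reported. Let a and b be the assumed correlations of the two variables with such a third variable, within the sample. Age is used as the example, and a = b in size is varied from 0.2 to 0.5.

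**3. Formula.** Unadjusted r = partial r × sqrt((1 − a²)(1 − b²)) + ab. The chance of two-sided p < 0.05 comes from Fisher z with standard error 1/sqrt(60 − 3) = 0.1325.

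**4. No true relation, same sign (r = a²).**

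| a = b | Spurious r | Chance of p < 0.05, N = 60 |
|---|---|---|
| 0.2 | 0.04 | 0.061 |
| 0.3 | 0.09 | 0.105 |
| 0.4 | 0.16 | 0.230 |
| 0.5 | 0.25 | 0.487 |

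An age-adjusted test would stay at 0.05. A separate simulation with matched pairs and uniform age 12 to 18 gave 10%, 23% and 49% for the last three rows.

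**5. True partial r = 0.40, opposite signs (r = 0.40 × (1 − a²) − a²).**

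| Size of a, b | Unadjusted r | Power, N = 60 |
|---|---|---|
| 0.3 | 0.364 − 0.09 = 0.274 | 0.565 |
| 0.4 | 0.336 − 0.16 = 0.176 | 0.269 |
| 0.5 | 0.300 − 0.25 = 0.050 | 0.067 |

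Without any confounding, the power is 0.892.

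**6. Pooled pairs involving symptom severity.** The difference in BDI-II between patients and controls is unrelated to the matched variables, and it enlarges the variance. Assume group differences of 2 SD in symptoms and 0.8 SD in sleep, with within-group a = b = 0.4. The variances become 1 + 2²/4 = 2 and 1 + 0.8²/4 = 1.16, so the spurious part is 0.16/sqrt(2 × 1.16) = 0.105. It is smaller than 0.16 but not removed.

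**7. Cost of adjustment.** With three covariates the Fisher z standard error is 1/sqrt(60 − 3 − 3). Power for r = 0.40 at N = 60 goes from 0.892 to 0.876. By the same approximation, the N needed for 80% power goes from 47 to 50, still below 60.

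**The case against.** The strongest reply is that the article does not show the confounding. The cited passages link different outcomes to different variables:

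- The rise in depression from 8.4% to 15.4% across adolescence is lifetime prevalence in a survey. Participants here are enrolled by diagnosis with age-matched controls, so the figure says nothing about BDI-II severity by age within a group.
- The remark on sleep and development is general and is offered as a possible explanation of mixed findings.
- The passage on the cortisol awakening response and gender describes a control measure, and the luteal-phase schedule already reduces that part.
- No passage makes the awakening response depend on age or puberty, or alpha-amylase on age, puberty or gender.

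All of this stands. A reader might infer that, by the plan's own account, both sides of each correlation depend on the same variables; the text does not support that.

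A reader might also infer that the plan adjusts for covariates nowhere else. It names covariance analyses for the hormone outcomes, so the statement holds only for the correlations.

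The rates in the working are single-test rates under assumed values, not error rates of the plan after the false discovery rate correction. An unadjusted correlation also remains a fair description of co-occurrence, which is part of what the Aims ask. To say that these correlations cannot answer the study's questions would be too strong.

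One part of the reply does not stand, namely that adjustment is a detail for an analysis plan not shown. The article names the method as bivariate. A further plan could add adjusted analyses as a supplement, but making them the inferential analysis would change what is stated here.

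**Conclusion.** The point holds as a limitation of a stated choice, not as a demonstrated error. Unadjusted correlations over ages 12 to 18 and both genders cannot separate a direct relation from a shared developmental or gender gradient, and matching does not help with this. The protocol itself treats these variables as relevant, since it matches on them and schedules measurements around one of them.

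The size is unknown. It is negligible if the correlations with age are about 0.2. It is material only if both variables of a pair correlate at roughly 0.3 to 0.5 with the same third variable. It is smaller for pooled pairs with the BDI-II and, as regards gender, for pairs with the cortisol awakening response. The rates assume N = 60. Within a group of 30 the bias in r is the same, and the excess of significant results is smaller.

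The relational aims and the secondary outcome are affected. The primary group contrasts are not. Because the remedy uses data already collected and costs almost no power, the change is worth making.

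**What to change.** In the Statistical analysis section, make partial correlations (rank-based if the data are skewed), or equivalent regressions, adjusted for age, gender and PDS score the inferential analysis of these relations. Apply the false discovery rate correction to the adjusted p-values. Show the bivariate correlations alongside as descriptive.

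The cost is one sentence, three degrees of freedom and the small loss of power shown above. Age and PDS score overlap, so their separate contributions should not be interpreted. That does not matter when both serve only as adjustment.

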## Discussion

### Knowledge gains

Although sleep disturbance and cortisol release has been the object of broad research in the context of depressive disorders in past years,^70,16^ to the best of our knowledge, no study has examined the combination of subjective sleep quality, accelerometry measuring objective sleep quality, and neurohormonal correlates of HPA axis and autonomous nervous system activity in adolescents with depression before. With the results of our study, we aim to better understand how the strength and course of cortisol and alpha-amylase awakening responses, and subjective as well as objective sleep quality, are related in adolescents with depressive disorders. This present study design allows a wide-ranging approach to sleep impairment and the status of different physiological stress responses. Considering the importance of sleep in the process of growth and maturation, this knowledge is urgently needed to enhance the perspective for adolescent patients with depression, and to integrate sleep quality more profoundly into the treatment process.^34,7,6^

### Relevance of the study

The major value of this study is its contributions toward clinical practice and patients with depressive disorders. In the recruitment process for patients with depression, we receive valuable feedback from both patients and legal guardians about the relevance and level of suffering sleep impairment causes for adolescents with depression. In clinical practice, the urgent demand for targeted assessment strategies and adequate treating to reduce patients’ suffering becomes apparent. Moreover, practising therapists and physicians are frequently confronted with the topic of sleep impairment, but current research on the characteristics of these sleep concerns, the actual amount of objective disruption and subjectively experienced impairment, and especially its effects on different physiological stress systems, does not meet patients’ needs. Previous studies and meta-analyses have repeatedly confirmed these deficits.^6,7,34,71^ The results of the current study are of great value to better our understanding of the origin and overall impact of impaired sleep quality. Moreover, the findings can be a useful reference point for the development of sleep assessments and sleep diaries, which particularly meet the needs of adolescent patients with depressive disorders.

In the pathophysiology regarding trigger and recurrence of depressive disorders, CAR seems to constitute a promising and highly relevant biomarker linked to coping and daily hassles.^22^ An increased CAR in healthy adolescents might be a useful mechanism to adjust to temporarily increased daily demands and to reduce the individual stress level.^22^ A potential dysregulation of this pathomechanism could be highly relevant in the context of stress and occurrence of depressive symptoms.^31^ Because of these previous findings, we added the SSKJ 3-8 R questionnaire to our assessment, which examines vulnerability to daily hassles and the use of various coping mechanisms.^51^

In the context of stress, salivary alpha-amylase has been shown to have a sensitive response to acute stress situations,^22^ with a potentially higher specificity for depressive disorders.^23^

Considering that the onset of depressive symptoms is often linked to a major or minor stressful event,^31^ the examination of pathophysiological aspects of these stress-related biomarkers in adolescents with depressive disorders is essential. By examining the neurohormonal correlates, we aim to contribute to the examination of the relationship between the hormonal system and sleep quality of adolescents with depressive disorders.

All participants in this study will benefit from a detailed and technically supported analysis of sleep quality, which exceeds the diagnostic standard in depressive disorders by far.

### Strengths and limitations

One particular strength of our study is the domestic sleep setting. with its simple and non-invasive accelerometry measurement, which preserves the familiar sleeping habits and allows us to assess sleeping measurements with as little distortion as possible.^9,71^ By choosing out-patients or day patients for the index group, we strive for an undisturbed and natural sleeping condition,^10^ to achieve generalisability of the study findings. Additionally, the combination of an accelerometry measurement and CAR as well as alpha-amylase measurements after awakening provides the benefit of an objective validation of awakening, which is a useful verification for the saliva sampling times.^32,23^ Another strength is the broadness of objective and subjective measurement methods combined with the assessment of both HPA axis and autonomous nervous system activation,^7^ which is, to our knowledge, a rare approach in research focusing on adolescent patients with depression.^24^ With the heterogeneous findings of previous sleep research in adolescent patients with depression^7,11^ and the unexplored potential of alpha-amylase as a useful addition to cortisol-based stress research,^22^ the findings of this study can be of great value to the consideration of depression and physiological stress conditions and its consequences, and may stimulate further research.

A considerable limitation of this study is the exclusion of adolescents with depression who are on antidepressant medication in favour of saliva sampling and including only out-patients and day patients. These eligibility criteria may shift the examined cohort to less severe courses of depressive diseases and exclude long-term and severely ill patients who often take antidepressant medicine or undergo in-patient treatment. Nevertheless, with a prompt study advertisement and a contemporary study appointment, we are able to include a wide range of depression severity before medication intake or in-patient admission is decided. An additional limitation is that external interfering factors disturbing participants’ sleep cannot be controlled in the domestic surrounding during the measurement week. However, these external influences are unavoidable when data is collected in the natural surroundings and under everyday conditions. Subjective sleep impairment in adolescents with depression is mostly experienced within their home environment, thus examining sleep quality, including all external influences, is crucial for a realistic and reliable assessment, and leads to a high ecological validity. Finally, measurements of sleep and salivary biomarkers are limited to 1 week or 3 days, respectively, which implies a certain variability in the course of disease and external influences. Nonetheless, the 3-day saliva sampling and the 1-week sleep measurements constitute a detailed and wide-ranging assessment compared with previous assessments,^30^ and can therefore be considered reliable.

Despite the aforementioned limitations, this study adds crucial and multifactorial value to the pre-existing research in sleep and stress research in adolescents with depressive disorders. In addition, the results of our study could make an important contribution in the establishment of an ambulatory assessment of sleep quality and continuous observation of sleep impairment in the course of disease in adolescents with depressive disorders.

### Trial status

Recruitment has started on 1 February 2021, and the study is intended to be completed by February 2022.

## Data Availability

The data-sets used and/or analysed during the current study are available from the corresponding author, [name], on reasonable request.
